Recently, a model was developed and validated to predict delirium in ICU patients [18]. With this model, the effectiveness of preventive strategies can be compared in different groups that differ in *a priori* risk of delirium. This delirium prediction model was used to identify high-risk ICU patients (i.e., *a priori* risk of delirium >50%). Compared to a historical control group, prophylactic low-dose haloperidol was associated with better delirium related outcomes. In this high-risk group (>50%) of critically ill patients, incidence of delirium was significantly lower in the preventive treatment group (65%), compared to the control group (75%). Furthermore, haloperidol prophylaxis was associated with a hazard rate of 0.8 for 28-day mortality [19]. However, because of the pre-/post-implementation design of this trial, other factors that may have changed between the study periods may have influenced these findings. Nevertheless, the results suggest that prevention of delirium might be beneficial in critically ill patients. Since no relevant side effects associated with the administration of a low dosage of haloperidol were reported in the prophylactic studies [11,12,17,19], it is conceivable that a higher dose of haloperidol may exert more pronounced beneficial effects. Furthermore, the optimal dosage of haloperidol in critically ill patients, as well as the occupancy levels of dopamine-2 receptors and sigma-1 receptors when administering haloperidol, remain unknown. Therefore, in the present study proposal the effects of two dosages of haloperidol versus placebo will be determined.

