Given the fact that the development of delirium can be predicted only 24 h after ICU admission, and the clear relation between time to treatment with haloperidol and the duration of delirium [19], initiation of prophylaxis as early as possible is warranted. Based on our historical data, the median predicted risk of delirium is approximately 35% in patients with an expected stay on the ICU of over one day; this is considered a high risk for delirium development. A clinical estimation of an ICU LOS >1 day is possible within the first few hours after ICU admission. Previous studies that included patients using similar criterion of an expected ICU LOS were found feasible [20,21]. Therefore, the clinical estimation by the attending ICU-physician of an ICU LOS >1 day will be used as an inclusion criterion for this study, in which the prediction to develop delirium (using the PRE-DELIRIC model [18]) will be used to facilitate post-hoc analyses to investigate which patients benefit most from prophylactic therapy. By using the PRE-DELIRIC score as an *a priori* determined post-hoc analysis, we will learn if the putative beneficial effect of haloperidol is related to the risk to develop delirium, or comparable in all patients, independent of the baseline risk to develop delirium. In addition, it will facilitate the determination of a cut-off level for the PRE-DELIRIC score.

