	- death that is not related to the underlying disease or sequel of the underlying disease, or death that is considered by the investigator to be related to study drug
	- prolonged inpatient hospitalization or re-hospitalization
	- a life-threatening experience (that is, immediate risk of dying)
	- persistent or significant disability/incapacity
	- congenital anomaly/birth defect
	- considered significant by the investigator for any other reason
*Sudden unexpected serious adverse reactions*	Unexpected adverse reactions are adverse reactions, of which the nature, or severity, is not consistent with the applicable product information. Adverse reactions are all untoward and unintended responses to an investigational product related to any dose administered.

#### **
*Primary objective*
**

To determine the effect of prophylactic haloperidol use on 28-days survival.

#### **
*Secondary objectives*
**

There are seven secondary objectives:

1. To determine the effect of prophylactic haloperidol use on 90-day survival; survival analysis stratifying for delirium incidence will be performed.

2. To determine the effect of prophylactic haloperidol use on the incidence of delirium.

3. To determine the effect of prophylactic haloperidol use on the number of delirium- and coma-free days in a period of 28 days.

4. To determine the effect of prophylactic haloperidol use on delirium related outcomes: time to successful extubation, incidence of re-intubation, incidence of ICU readmission, and incidence of unplanned removal of tubes and catheters.

5. To evaluate the incidence and severity of side effects of haloperidol prophylaxis.

6. To determine the effect of preventive haloperidol use on quality of life 1 and 6 months following ICU admission compared with a baseline measurement at ICU admission using the Short Form-12 (SF-12) questionnaire.

7. *A priori* defined post-hoc analyses:

a. To determine the preventive effectiveness of haloperidol in different patient groups based on the *a priori* risk to develop delirium: patients with a predicted risk up to 50%, 50–70%, 70–90%, above 90% will be evaluated.

a. To determine the preventive effectiveness of haloperidol in different patient groups: medical/surgical/trauma patients, per acute physiology and chronic health evaluation-II (APACHE-II) score (<20, 20–25, >25)

a. Effectiveness of prophylaxis when delirium is diagnosed based on 1, 2, or more days with positive CAM-ICU scoring.

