Furthermore, subgroup analysis will be performed by direct comparisons of *a priori* specified subgroups, i.e., predicted risk group, admission type group, and APACHE-II group, in order to determine effectiveness of prophylactic haloperidol treatment in these subgroups on 28-day survival.

All statistical tests are two-sided and statistical significance is defined as a *P* value < 0.05. All data will be analyzed using SPSS version 20.01 (SPSS, Chicago, IL, USA).

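### The PRE-DELIRIC bands are first cut at 50% although the expected median risk is about 35%, and the planned subgroup analysis does not commit to testing whether the effect changes with risk

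*Protocol article*

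**What the plan says.** The Background (Protocol article) states that "the median predicted risk of delirium is approximately 35% in patients with an expected stay on the ICU of over one day" and regards that level as high risk. Expected stay of over one day is also the inclusion criterion.

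The Background gives the PRE-DELIRIC analysis three purposes:
- "to investigate which patients benefit most from prophylactic therapy";
- to learn whether a benefit is "related to the risk to develop delirium, or comparable in all patients, independent of the baseline risk to develop delirium";
- "it will facilitate the determination of a cut-off level for the PRE-DELIRIC score".

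The closing paragraph of the Background makes relating benefit to prior risk the second aim. The Discussion expects to report the risk category in which prophylaxis works best.

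The groups are set in Objectives, secondary objective 7, and again in Table 2: "patients with a predicted risk up to 50%, 50–70%, 70–90%, above 90% will be evaluated". In the statistics section, "subgroup analysis will be performed by direct comparisons of" the pre-specified subgroups is planned, in "order to determine effectiveness of prophylactic haloperidol treatment in these subgroups on 28-day survival".

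**The concern.** The first cut lies above the expected median. Three of the four bands divide the range above 50%, and the range where most patients are expected is left whole. A patient at 5% predicted risk and one at 35% are analysed together, although the article uses the 35% figure to justify enrolment.

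The question is also one of effect modification, while the stated purpose of the analysis is effectiveness in each group. If bands are read by their own significance, a chance pattern can pass for a finding about who benefits, and a threshold in the lower half of the risk range would go unseen. The trial's second aim is at stake. The primary comparison is not affected.

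**Working it through.** **1. Share in the lowest band.** Inputs: median risk about 35% (Background); 2,145 patients, 715 per group (Abstract). At least half of the patients lie at or below the median, and the median is below 50%. So the lowest band holds at least 2,145 / 2 ≈ 1,072 patients, whatever the shape of the distribution. The three upper bands share at most about 1,072, which is on average at most 1,072 / 9 ≈ 119 per arm and band.

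**2. Shares above 50%.** The article does not give them. Two assumed families with median 35% show the range:

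| Assumed distribution | up to 50% | 50–70% | 70–90% | above 90% |
|---|---|---|---|---|
| Beta, a+b = 1.5 | 62.5% | 15.1% | 14.4% | 8.0% |
| Beta, a+b = 3 | 68.6% | 19.0% | 10.8% | 1.6% |
| Beta, a+b = 8 | 79.7% | 17.9% | 2.4% | 0.0% |
| Logit-normal, SD 0.8 | 78.0% | 18.6% | 3.3% | 0.0% |
| Logit-normal, SD 1.5 | 66.0% | 17.6% | 13.4% | 3.0% |

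**3. The plan's event count.** Schoenfeld's formula for hazard ratio 0.85, 80% power and two-sided 5% gives 4 × (1.96 + 0.8416)² / (ln 0.85)² = 1,189 events for one dose against placebo. With exponential survival, a control median of 18 days, 90 days of accrual and 28 days of follow-up, the event probabilities are 0.905 and 0.932 (hazard ratio taken in the direction worded). Then 1,189 / 1.837 = 647 per group, which is the stated figure.

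The Abstract's 12% placebo mortality implies far fewer events. With 1 − 0.88^0.85 = 0.103 in the treated group, 1,430 × (0.12 + 0.103) / 2 ≈ 159 deaths. The two inputs do not agree with each other, so both counts are used below.

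**4. What significance within bands shows.** Suppose the hazard ratio is 0.85 on both sides of 50%, so there is no effect modification, and events split equally.
- 1,189 events: each side has about 594. √594 × 0.1625 / 2 − 1.96 ≈ 0.02, so power is 51% per side. The chance that exactly one side is significant is 2 × 0.509 × 0.491 = 50%. With 30% of events above 50% it is 55%.
- 159 deaths: each side has about 80, power is 11% per side, and exactly one side is significant with probability 2 × 0.109 × 0.891 = 19%.

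A split result is thus common although the effect is the same in everyone.

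**5. What an interaction test could detect.** For a contrast at one cut, SE(log ratio of hazard ratios) = √(4/d₁ + 4/d₂), and 80% power needs 2.80 × SE.
- 159 deaths, equal split: SE = √(8/79.7) = 0.317; detectable ratio exp(−0.888) ≈ 0.41. With 30% of deaths above the cut it is 0.38. An equal split is the best case for a given total.
- 1,189 events, equal split: SE = √(8/594.5) = 0.116; detectable ratio exp(−0.325) ≈ 0.72.

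**The case against.** The 50% cut has a stated origin. The earlier study defined high risk that way ("risk of delirium >50%). Compared to a historical control group, prophylactic low-dose haloperidol was associated with better delirium related outcomes"), and separating patients like those from the newly included lower-risk patients is defensible. That justifies having a cut at 50%. It does not justify having none below it in a population with median 35%.

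Comparing subgroups directly can be read as comparing them with each other, and a statistical analysis plan that is not shown may specify an interaction test. This stands. The article is ambiguous on the method, and the mere absence of an interaction term from a condensed article would be no finding. The cut-points, however, are fixed here twice, and the stated purpose is effectiveness in the subgroups.

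A reader might infer more than the article supports:
- That patients below 50% are left out. They are not: the lowest band includes them, undivided.
- That the upper bands are nearly empty. No shares are given. Under the assumptions above, 50–70% still holds about 15–20% of patients; only the top band may be very small, and that depends on the assumed distribution.
- That deaths per band can be forecast. This would need 12% mortality in every band, which is doubtful because the Background links delirium with higher mortality.
- That the second aim cannot be met. The score is collected for all patients (Data collection), so a better analysis remains open, and contrasts at 50, 70 and 90% are possible.

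**Conclusion.** The point holds as a mismatch between a declared aim and the analysis written for it. From the article's own median, at least half of the patients sit in one undivided band, and the listed bands cannot show a cut-off below 50%. This needs no further assumption. The figures of about 62–80% in the lowest band and 0–8% above 90% do rest on assumed distributions.

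The wording does not commit to a test of whether the effect changes with risk, and significance within bands is no substitute for one. The 50% and 19% chances of a split result assume a common hazard ratio of 0.85 and an equal division of events.

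The wording should be changed, but the consequence is limited to a secondary, exploratory objective.

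**What to change.** State that the risk analysis is a treatment-by-PRE-DELIRIC interaction in the Cox model for 28-day survival, for each dose against placebo, with the score kept continuous. Report the estimated effect across the risk range with confidence intervals and the interaction test. Keep bands for description only, cut at quantiles of the observed score or with added cuts below 50%.

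This costs a change of wording and no new data. The four listed bands lose their role as the main analysis; a 50% cut can stay as a descriptive link to the earlier study. The change does not cure low power. At 12% mortality even an equal split detects only a ratio of hazard ratios near 0.41 with 80% power, so the result should be labelled exploratory and a non-significant interaction should not be read as evidence of a uniform effect.

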### Randomization

Block randomization will be applied by the pharmacist. The randomization numbers are coupled with the Clinical Report Form (CRF) number and the number of study medication box. Boxes are numbered and consist of 12 ampoules of study drug. If necessary, when a patient is admitted to the ICU for more than 4 days and is not delirious, a new box will be assigned to this patient consisting of the same study regime as the previous box. All study medication will be manufactured by the Department of Clinical Pharmacy of the Radboud University Nijmegen Medical Centre, which holds a Good Manufacturing Practice certificate. Ampoules of study medication consist of 1 mg/mL or 2 mg/mL haloperidol or 1 mL sodium chloride 0.9% solution, all with a total volume of 1 mL. The randomization code is kept by the pharmacist and will be broken only if necessary for safety reasons. Only the pharmacist of the Radboud University Nijmegen Medical Centre is unblinded for this study.

### Intervention and control group

This study involves a comparison of prophylactic haloperidol in a dosage of 1 mg (intervention group 1) or 2 mg (intervention group 2) administered as a bolus intravenously three times a day compared with placebo of 0.9% sodium chloride (control group) administered intravenously three times a day in a double-blind fashion. All ampoules and drug boxes have an identical appearance.

To decrease the likelihood of encountering side effects in specific cohorts, the dose of the study drug will be halved in patients aged ≥80 years, weighing ≤50 kg, suffering from liver failure (indicated by serum bilirubin level >50 μmol/L) present at time of inclusion or during the study. Patients with an adjusted dose remain allocated to their original group (intention-to-treat).

Patients with an adjusted dose remain allocated to their original group (intention to treat).

### End of study medication

Prophylactic treatment with haloperidol will be continued until day 28, or discharge from the ICU (whatever comes first), or until delirium occurs. In the latter case, patients will be subsequently treated according to the delirium treatment protocol (with higher dosage of open label haloperidol).

In case delirium occurs, the patient’s study medication (prophylaxis treatment) will be stopped and the patient will be treated with open label haloperidol according to the delirium treatment protocol described below. Analysis will be on intention-to-treat basis. Study medication will not be restarted once delirium subsides, therapeutic haloperidol is stopped, or when a patient is re-admitted to the ICU within 28 days.

#### **
*Delirium treatment*
**

Patients with delirium (defined as a positive CAM-ICU test) will be treated with 2 mg haloperidol intravenously three times daily. Patients suffering from *hypoactive* delirium (only RASS scores between 0 and -3) and patients aged ≥80 years, weighing ≤50 kg, or with liver failure, will be treated with a lower dosage of 3x1 mg intravenously. Dosage can be increased up to a maximum of 3x5 mg in case of serious agitation or anxiety due to delirium. Additionally, midazolam, clonidine, propofol, or dexmedetomidine can be used as an escape therapy in case of serious agitation with insufficient efficacy of haloperidol according to usual patient care.

In patients treated for more than three days, the dosage will be halved when delirium subsides. When delirium does not reoccur the following day (CAM-ICU remains negative), the dosage will be halved again and then stopped the third day when the patient remains non-delirious. In case delirium occurs again during the reducing phase, the original dose will be restarted.

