### Data collection

All data will be collected electronically in an electronic CRF (E-CRF). The E-CRF is a secured website where the participating hospitals must login using a unique password. Participating hospitals will only have access to their own data.

Demographic variables will be collected from all patients, including age, gender, PRE-DELIRIC score, APACHE-II score, and diagnosis group. Furthermore, outcome related variables will be collected (Table 2) as well as variables that may influence the delirium outcome, i.e., dexmedetomidine [32] and early mobilization [33]. Concerning the study medication, we will collect data on the amount of study drug administered as well as open-label haloperidol and other anti-delirium drugs administered in case delirium occurs.

**Table 2 T2:** Primary, secondary endpoints and posthoc analyses

**Primary endpoint**	**Secondary endpoints**	**Post-hoc analyses**
28-day mortality	90-day mortality Delirium incidence	Effectiveness in groups of predicted risk up to 50%, 50–70%, 70–90%, above 90% will be evaluated
	Number of delirium and coma free-days in 28 days	Effectiveness in diagnosis groups: medical, surgical and trauma patients
	Duration of mechanical ventilation	Effectiveness per APACHE-II score: <20, 20–25, >25
	Incidence of unintended tube or catheter removal	Effectiveness in groups with 1, 2, or more positive CAM-ICU scores
	Incidence of ICU re-admission	
	Quality of life measured at time of ICU admission, after 1 and 6 months using SF-12	
	Incidence and severity of side effects of prophylactic haloperidol (all patients)	

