### Safety monitoring and safety issues

A Data Safety Monitor Board (DSMB) is established for this study to perform ongoing safety surveillance and to perform interim analyses on the safety data. This is an independent committee composed of two physicians/researchers (a psychiatrist and an anesthetist) and a statistician. The DSMB will perform all interim analyses. To assess side effects of haloperidol and to determine superiority of the intervention or placebo the DSMB will be unblinded for this study, while all researchers remain blinded. Furthermore, the study will be monitored by an independent researcher who will monitor the trial master file, and perform random checks of informed consent forms, drug accountability lists, and source data of primary and secondary outcome measures.

Concerning safety issues, during a patient’s treatment with the study medication, known side effects of haloperidol [34] are pro-actively collected with a special focus on prolonged QTc-time, drowsiness, extrapyramidal symptoms, and agitation and sedation effects. All side effects will be collected during patients’ treatment with the study medication until 24 h after stopping the study medication. In case of the occurrence of side effects, physicians can reduce the dosage or stop the study medication, depending on the severity of the occurred side effect and at the discretion of the attending physician. Only for prolonged QTc-time, strict stopping rules are applied, as described below. To detect side effects of haloperidol, the protocol dictates that patients are physically examined every day for known signs of extrapyramidal symptoms (signs of Parkinsonism and/or akathisia and/or dystonia). Furthermore, daily QTc-time is calculated using a 12-lead ECG or a monitor lead ECG. A QTc-time of over 500 msec combined with an increase of over 10% of baseline QTc-time is defined as prolonged QTc-time. In case of QTc-time prolongation, the study drug is temporarily stopped until QTc-time is normalized. After normalization of QTc-time (<500 msec) the study drug will be restarted. If QTc-time becomes prolonged again, the study drug will be stopped definitively. The patient will remain allocated to the original study group.

To determine long-term side effects, such as rigidity, and quality of life, a recommended and validated quality of life questionnaire, SF-12 [35], is taken at the time of admission and is sent to the patients 1 and 6 months after ICU admission.

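### The QTc hold and definitive stop cover only the blinded study drug; the printed open-label haloperidol regimen for delirium (3 or 6 mg/day, up to 15 mg/day) has no QTc exception

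*Protocol article*

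**What the plan says.** All references are to the Protocol article.

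**QTc rules.** Under 'Safety monitoring and safety issues', QTc is the one side effect with fixed rules: "Only for prolonged QTc-time, strict stopping rules are applied, as described below". Prolongation means a QTc above 500 msec together with a rise of more than 10% from baseline. The consequences are a temporary hold, a restart once QTc is below 500 msec, and a permanent stop if prolongation recurs. Each is worded for the study drug.

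**Delirium regimen.** Under 'End of study medication', delirium ends the study medication and the patient is then "treated with open label haloperidol according to the delirium treatment protocol described below". The standard dose is fixed: "Patients with delirium (defined as a positive CAM-ICU test) will be treated with 2 mg haloperidol intravenously three times daily". Patients with hypoactive delirium, aged 80 or over, weighing 50 kg or less, or in liver failure "will be treated with a lower dosage of 3x1 mg intravenously". There is a ceiling: "Dosage can be increased up to a maximum of 3x5 mg in case of serious agitation or anxiety due to delirium". Four other drugs are named (dexmedetomidine, propofol, clonidine and midazolam), with this condition on their use: "can be used as an escape therapy in case of serious agitation with insufficient efficacy of haloperidol according to usual patient care". A taper follows. QTc is not mentioned in this section.

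**Related text.** 'Intervention and control group' applies the same age, weight and liver cautions to the blinded drug: "the dose of the study drug will be halved in patients aged" 80 or over, and in the low-weight and liver-failure groups. 'Data collection' records "open-label haloperidol and other anti-delirium drugs administered in case delirium occurs".

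**The concern.** The article treats study medication and open-label haloperidol as two separate treatments, the second starting when the first stops. A rule written for the first does not, as worded, carry over to the second, although the molecule and route are the same.

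The regimen is also not left to another document. It is printed with starting doses, a ceiling, escape drugs and a taper, and it repeats three of the safety cautions that apply to the blinded drug. The caution for which the article sets strict rules is the one not repeated.

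Two kinds of delirious patient are affected:

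- one whose QTc meets the definition of prolongation when delirium is diagnosed or during its treatment;
- one whose study drug was permanently stopped for recurrent prolongation.

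For both, the trial withholds blinded drug at 0, 3 or 6 mg/day (less if halved), while its printed treatment rule starts open-label haloperidol and allows escalation. The Background describes ventricular arrhythmia on haloperidol as very rare but dose-related. What is at stake is the safety of these patients, not the validity of the comparison.

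**Working it through.** **Step 1: daily doses** (dose per administration × 3).

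- Blinded full dose: 3 × 1 = 3 mg/day and 3 × 2 = 6 mg/day. Halved: 1.5 and 3 mg/day.
- Open-label standard start: 3 × 2 = 6 mg/day. Reduced start: 3 × 1 = 3 mg/day.
- Open-label ceiling: 3 × 5 = 15 mg/day.

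**Step 2: open-label dose relative to blinded dose.**

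| Patient | Open-label dose | vs 1 mg arm | vs 2 mg arm |
|---|---|---|---|
| Standard, start | 6 mg/day | 6/3 = 2.0 | 6/6 = 1.0 |
| Hypoactive, full blinded dose, start | 3 mg/day | 3/3 = 1.0 | 3/6 = 0.5 |
| Aged ≥80, ≤50 kg or liver failure (blinded dose halved), start | 3 mg/day | 3/1.5 = 2.0 | 3/3 = 1.0 |
| Standard, ceiling | 15 mg/day | 15/3 = 5.0 | 15/6 = 2.5 |

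For a placebo patient, open-label treatment is the first haloperidol given in the trial. No start is higher than the corresponding dose in the 2 mg arm. Only escalation goes beyond the blinded range.

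**Step 3: which QTc provisions reach open-label haloperidol.**

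- Exclusion criterion (QTc above 500 msec): applies at entry only.
- Hold, restart and permanent stop: worded for the study drug.
- Discretionary reduction or stop for other side effects: worded for the study medication.
- Side-effect collection: ends 24 h after study medication stops. The regimen foresees delirium treatment lasting more than three days.
- Daily QTc calculation: the sentence is not itself limited to days on study drug, so measurement may continue.
- Serious adverse events, and data safety monitoring board reviews after 175, 350, 500 and 1,000 patients: these detect events but set no QTc action.

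No provision ties a QTc finding to withholding, reducing or stopping open-label haloperidol.

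**Step 4: the alternatives.** The printed condition for the escape drugs is serious agitation that haloperidol has not controlled. A patient who should not receive haloperidol because of QTc is not addressed.

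**Step 5: number affected.** The article gives no rate of QTc prolongation, first or recurrent, so the number cannot be derived and is not estimated.

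**The case against.** The strongest objection is that this is a journal article condensing a fuller protocol, and that holding criteria for rescue treatment are the kind of clinical detail a condensation drops. That limits certainty: the full protocol may contain the clause. It does not remove the point, because the article prints a specific regimen as a rule, and that rule, followed as written, leads to the result described.

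Second, the asymmetry can be defended. Blinded prophylaxis needs a mechanical rule because the physician does not know the dose and benefit is unproven. Open-label haloperidol has a known dose, is titrated at the bedside and treats established delirium. This supports leaving more to the physician, but the article does not say that QTc is to be weighed.

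Third, the Background expects no relevant side effects at 3x1 or 3x2 mg, whatever the underlying condition or co-medication. That covers every open-label starting dose, but not escalation above 6 mg/day. The entry exclusion for QTc and recent ventricular arrhythmia narrows the subgroup further.

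Four stronger readings are tempting, and the article does not support them:

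- *QTc goes unmeasured during open-label treatment.* The daily QTc sentence is not restricted to study-drug days; the gap is in action, not necessarily in measurement.
- *Other treatment is forbidden.* It is not, and recording other anti-delirium drugs implies some latitude.
- *Any patient with a past QTc episode is affected.* The trial itself accepts re-exposure below 500 msec after a single episode, so those patients are outside this point.
- *The two sections contradict each other.* They govern different treatments; one simply lacks the other's safeguard.

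**Conclusion.** The point holds as an inexpensive safety improvement. As printed, the QTc hold and permanent stop protect patients only from the blinded drug, while every CAM-ICU-positive patient is directed to open-label haloperidol without a QTc exception. That includes patients with current prolongation and patients whose study drug was permanently stopped for recurrent prolongation.

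Its size is modest. The subgroup is probably small and its number is unknown. Starting doses stay within the blinded range, so the concern is greatest for escalation above 6 mg/day. The 2.5-fold and 5-fold ratios describe the printed ceiling and do not measure risk in these patients.

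A reader might infer that the trial's results are compromised. Nothing here supports that: no effect on bias, power or type I error is claimed.

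The conclusion rests on reading 'study drug' in the safety section as the blinded medication, which is how the article uses the term, and on the full protocol, which is not shown, not already containing the rule.

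**What to change.** Add to 'Delirium treatment' wording such as:

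*Open-label haloperidol is not started, or is held, while QTc is prolonged as defined in the safety section (above 500 msec with a rise of more than 10% from baseline). After a definitive QTc stop of study drug, it is given only at a QTc below 500 msec and by decision of the attending physician. When haloperidol is withheld for QTc, the listed alternatives may be used without first showing that haloperidol is insufficient.*

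This reuses the trial's own definition and restart threshold and changes no endpoint, randomised dose or analysis. The cost is a few sentences, and a few delirious patients will receive haloperidol later or receive another drug. Unless daily QTc readings currently stop with the study drug, which the article does not say, no extra readings are needed. If the full protocol already has this rule, confirming it is enough.
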